### Sample size and power calculation

Participants will be 264 males, relatives of women with BRCA1 and/or BRCA2 germline mutations who are patients of the Division of Cancer Prevention and Genetics at the European Institute of Oncology (IEO) in Milan. The IEO is a specialized Hospital and an internationally recognized Cancer Center located in Italy working on research, prevention, diagnosis, and treatment of cancer.

The sample size is determined through an a priori power analysis using GPower 4.0 [51]. Among the imputed parameters it was chosen to include partial η2 = .05, alpha lower than .05, power d (1-B) = .70. Considering that Luszczynska et al. [52] found a η2 = .01, η2 = .05 is a prudential choice. Two groups, corresponding to the two experimental conditions of the study, and 7 covariates were included. The final estimated number of participants is 132, 66 in each group. It should be noted that changing the number of covariates does not change the total number of participants. As of the date of submission of this research plan for preregistration, the data have not yet been collected, created, or realized.

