#### Time 1 assessment

All participants will complete the T1 assessment, via an online survey which will be available for a two-week period. The T1 measures will include demographic, health status, risk perception, health risk aversion, and intolerance of uncertainty. After this evaluation, participants will be randomized and exposed to one message. A manipulation check, the evaluation of the perceived quality of the information presented on the messages, positive outcome expectations, action self-efficacy, benefit for genetic test will be then collected. The constructs of trust in doctors and health literacy included in the original study protocol approved by the Ethical Committee have been not integrated here.

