### Primary and secondary outcomes

The primary objective of the present research project is to compare self-referred message to family-referred message promoting men’s adherence to evidence-based guidelines on *BRCA1/2* germline genetic testing. The primary clinical objective is to determine what is the best communication strategy to inform men who are at risk to have a germline mutation because they are relatives of women with such a mutation. The primary hypothesis of the study is that family-referred narrative gain framed message (vs. self-referred narrative gain framed message) will produce greater intention and action to undergo genetic testing for *BRCA 1/2* germline mutations in at-risk men.

The secondary objective is to assess men’s characteristics (demographic information, psychological characteristics, health status) that may explain the intention and the action to undergo genetic test for BRCA germline mutations.

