### Statistical analyses

Data exclusion: The answers to the manipulation check will be analyzed before the main analyses to see whether participants have read the message until the end, understood, and recalled the content.

Missing data: presence of missing data will be checked before conducting the main analyses. If a subject does not complete T1 and T2 that subject will be excluded from the analysis.

Normality of the data will be checked before conducting the main analyses. Non-normality will be handled applying either non-parametric tests or SEM with estimator for non-normal distribution.

Statistical analyses will be performed in SPSS version 25 and the *Lavaan* and *SemPaths* packages in RStudio software.

Preliminary analysis: Pearson’s r correlations among variables.

Main analyses: the hypotheses 1, 2, 3, and 4 will be tested either using structural equation modeling (SEM) or multiple regressions. Research question 1 will be tested either using structural equation modeling (SEM) or ANOVA. In case of non-normality in the data, WLSMV will be applied and the Satorra-Bentler scaled test statistic and robust standard errors were used. In the model specification, the factor loading of the first indicator of each latent variable will be set to 1. The following goodness-of-fit indices will be used to evaluate model-data correspondence: the Chi-square value, the Comparative Fit Index (CFI), and the Root Mean Square Error of Approximation (RMSEA). The model will be considered as acceptable when the CFI is higher than .90 and close to .95 and when the RMSEA is .08 or less. Finally, modification indices and the matrix of standardized correlation residuals will be inspected for potential improvement of model fit. Direct, indirect (or mediate), and total effects were also estimated. To test hypothesis number 5 an ANCOVA will be applied.

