**Hypothesis 1.** Predictors will be: risk perception, positive outcome expectations, action self-efficacy. Covariates: demographic, health status. Outcome variable will be: intention to undergo genetic test for BRCA germline mutations.**Hypothesis 2.** Predictors will be: health risk attitude, intolerance to the ambiguity. Covariates: demographic, health status. Outcome variables will be: intention to undergo genetic test for BRCA germline mutations, action and coping planning, action initiation.**Hypothesis 3.** Predictors will be: intention to undergo genetic test for BRCA germline mutations, coping self-efficacy. Covariates: demographic, health status. Outcome variables: action and coping planning.**Hypothesis 4.** Predictors will be: action and coping planning. Covariates: demographic, health status. Outcome variable: action initiation.**Research question 1.** Predictor variable: positive outcome expectations (personal vs family). Outcome: intention to undergo genetic test for BRCA germline mutations.**Hypothesis 5.** Predictor variable: treatment/message (family-referred narrative gain framed message vs. self-referred narrative gain framed message). Outcome variables: intention and action to undergo genetic testing for *BRCA 1/2* germline mutations.

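### The primary message comparison (HP5) is called an ANCOVA and was powered with 7 unnamed covariates, but its model statement lists none, so no covariate set is fixed

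*Protocol article*

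**What the plan says.** Four places in the protocol article bear on the HP5 model.

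- **Primary and secondary outcomes** makes the message comparison primary: "The primary hypothesis of the study is that family-referred narrative gain framed message (vs. self-referred narrative gain framed message) will produce greater intention". The sentence goes on to include action as well as intention.
- **Statistical analyses** names the method: "To test hypothesis number 5 an ANCOVA will be applied".
- **Sample size and power calculation** gives the inputs "partial η2 = .05, alpha lower than .05, power d (1-B) = .70" and adds: "Two groups, corresponding to the two experimental conditions of the study, and 7 covariates were included". The seven are not identified.
- **Statistical analyses, hypothesis list** gives HP5 as "Predictor variable: treatment/message (family-referred narrative gain framed message vs. self-referred narrative gain framed message). Outcome variables: intention and action to undergo genetic testing". There is no covariate entry. HP1 to HP4 each have one, for example HP4: "Predictors will be: action and coping planning. Covariates: demographic, health status. Outcome variable: action initiation".

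On what is available before the message, **Time 1 assessment** says: "The T1 measures will include demographic, health status, risk perception, health risk aversion, and intolerance of uncertainty". Randomisation and message exposure follow these measures. Positive outcome expectations and action self-efficacy are collected in the same T1 session, but after the message. Intention is first asked at T2.

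**The concern.** An ANCOVA with no covariate is a two-group ANOVA, so the HP5 statement does not match the method named for it or the calculation that sized it. It is also the only numbered hypothesis without a covariate entry, and it is the primary one.

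Two things are at stake.

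- **Precision.** Intention has no baseline value. The best available adjusters are therefore the pre-randomisation measures that the protocol itself expects to predict it: risk perception (HP1), and health risk attitude and intolerance of uncertainty (HP2).
- **An open choice.** The Blinding section says that those who analyse the data will know the allocation, so a covariate set not fixed in advance could be chosen with the arms known. The T1 label is no safeguard, because outcome expectations and action self-efficacy are also T1 measures but follow the message. The two messages differ in personal versus family benefit, which is what the outcome-expectation items measure. Adjusting for those items could remove part of the effect under test.

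Action falls under the same ANCOVA, although the T3 measures describe it as an event: an appointment made and a test received.

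**Working it through.** **1. Covariate entries side by side (hypothesis list)**

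| Hypothesis | Covariates listed |
|---|---|
| HP1 | demographic, health status |
| HP2 | demographic, health status |
| HP3 | demographic, health status |
| HP4 | demographic, health status |
| HP5 (primary, ANCOVA) | none |

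The Measures section has five demographic items (age, education, occupation, degree of relationship, household composition) and two health-status items (general health, chronic disease). Since 5 + 2 = 7, these may be the 7 covariates of the power analysis. That is an inference; the document does not say so.

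**2. The plan's own sample size**

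Inputs from the power section: partial η² = .05, α = .05, power .70, two groups, 7 covariates. The test is an F test with 1 numerator degree of freedom.

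- f² = .05 / .95 = .0526
- λ = f² × N
- error df = N − 2 − number of covariates
- power = 1 − noncentral F cdf at the 5% critical value

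The smallest N for power .70 is 120 (λ = 6.32, power 0.702). The stated 132 is not reproduced, which is a separate matter. N is 120 with 0, 1 or 7 covariates, so the protocol is right that the covariate count does not change it. With 7 covariates, power is 0.744 at N = 132 and 0.960 at N = 264.

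**3. If η² = .05 is the unadjusted effect and baseline covariates are added**

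Covariates explaining a share R² of the within-group variance of intention give f²(adjusted) = f² / (1 − R²). R² is assumed. With 7 covariates:

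| R² (assumed) | f² adjusted | Power, N = 132 | Power, N = 264 |
|---|---|---|---|
| 0 | .0526 | 0.744 | 0.960 |
| .09 | .0578 | 0.783 | 0.973 |
| .25 | .0702 | 0.855 | 0.990 |

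**4. If partial η² = .05 is already the adjusted effect and no covariates are used**

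Then f²(unadjusted) = f² × (1 − R²), with 0 covariates:

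| R² (assumed) | f² unadjusted | Power, N = 132 | Power, N = 264 |
|---|---|---|---|
| 0 | .0526 | 0.744 | 0.960 |
| .10 | .0474 | 0.699 | 0.941 |
| .20 | .0421 | 0.648 | 0.913 |

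**5. Cost in degrees of freedom**

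To the 7 items add three risk-perception items, one health risk attitude score and two intolerance-of-uncertainty dimensions: 7 + 3 + 1 + 2 = 13. At N = 132 and f² = .0526, power is 0.7438 with 7 covariates, 0.7435 with 13 and 0.7432 with 18, the last leaving room for dummy-coded categories. The loss is below 0.001.

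**The case against.** The strongest reply is that the passages, read together, show an intention to adjust. The same section allows ANOVA for research question 1 and names ANCOVA for HP5, which looks deliberate, and the power section counts 7 covariates. On that reading the list was left out rather than rejected, and an article may leave such a list to a fuller document. The first part stands. A reader might infer from the hypothesis list that HP5 is meant to be unadjusted and that the baseline measures will go unused; the documents do not support that. The second part carries less weight, because this article gives covariates for the other four numbered hypotheses and omits them only for the primary one.

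The reply on size also largely stands.

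- A partial η² in an ANCOVA is normally net of covariates, so step 4 is at least as natural a reading as step 3.
- No R² is given, and HP1 and HP2 are hypotheses, not evidence of prognostic strength.
- At N = 264 and η² = .05, power is already 0.96, leaving little to gain. A larger gain could be shown only with a smaller effect chosen by the reviewer.

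Nothing in the document proposes a post-message scale as an HP5 covariate. The only set it names, demographic and health status, is measured before randomisation. The hazard lies in the open choice, not in a stated plan.

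Finally, adjusting a logistic model changes the odds ratio being estimated, and many terms with few events can be unstable. Both are fair limits on the remedy.

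**Conclusion.** The point holds as an inconsistency in the primary model: ANCOVA is named, 7 unidentified covariates are assumed for power, and none is listed in the specification. It does not show that adjustment was ruled out, that precision will be lost, or that the sample size is wrong because of it.

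The size depends on which effect η² = .05 describes and on an R² that the document does not give. As an unadjusted effect with assumed R² of .09 to .25, adjustment is worth about 4 to 11 percentage points of power at N = 132 and 1 to 3 at N = 264. As an adjusted effect, dropping the covariates brings power at N = 132 to just under the planned .70 at R² = .10 and to 0.65 at R² = .20. Applying ANCOVA to action, if that is recorded as test taken or not, is a further mismatch of method and outcome.

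The correction is worth making before data are seen, since it settles the primary analysis at little cost.

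**What to change.** - **Intention.** Specify HP5 as an ANCOVA of intention on message arm, adjusted for a short fixed set measured before randomisation: the demographic and health-status set already named for HP1 to HP4, plus T1 risk perception, health risk attitude and intolerance of uncertainty. State how each is coded.
- **Exclusions.** State that no post-message measure enters the model, naming outcome expectations and action self-efficacy.
- **Power section.** Name the covariates, make their number agree with the model, and say whether η² = .05 is the adjusted or the unadjusted effect.
- **Action.** Analyse test taken or not by logistic regression with pre-randomisation covariates, using fewer if events are few.

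The cost is a change of wording, a few error degrees of freedom (under 0.001 of power in step 5), and an odds ratio for action that is conditional on the covariates and should be reported as such.

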## Discussion

The present research intends to evaluate what are the psychological determinants of men’s informed decision-making about genetic tests for *BRCA1/2* germline mutation. Another aim is to test two messages, one focused on the self and one on the family, regarding their capability to inform and persuade men. For these purposes, an experimental study with a longitudinal component will be developed.

Men face *BRCA*-related cancer risks as women do and they may also transmit their mutations to their children. Notwithstanding, men have not received much attention for now. They are under-tested compared to women and the communication is not tailored on their needs [58]. This consideration leads to the need to understand how male relatives of women with *BRCA1/2* germline mutations are motivated to protect themselves and others [13].

The results of the present research provide answers related to the immediate impact of several psychological variables, such as risk perception, positive outcome expectations, self-efficacy have on men’s intention, planning, and action initiation. All those variables are included in the HAPA model which is a well-known theory in the field of health psychology explaining motivational, volitional, and behavioral processes leading to health behavior changes [17, 18, 59]. The study will also analyze the role of health risk aversion and intolerance of ambiguity, which are variables linked to decision-making in health domains [31–34, 37, 60]. Finally, the research will inform regarding the effectiveness of two messages tailored on the specific men’s needs and focused one on the self and one on the family.

Data gathered from this study may inform health care providers, policy makers, and public health managers about the psychological variables implicated in the decision-making and the best communication strategies considering the various stages of changes, health risk aversion, and intolerance to the ambiguity. The study will give knowledge on how to modulate messages for the male population aimed at informing their decision-making and will guide genetic counsellors [61] for future interventions.

A good communication strategy may induce men to overcome their fear of stigmatization and to seek for information, since one of the most important barriers for men is the lack of knowledge about *BRCA1/2* germline mutations and their consequences. Moreover, it may also induce them to protect themselves and other family members by asking for genetic counseling. The present research tested two gain framed narrative messages written in the first-person vs. third person/family. Therefore, results from the present research will make it possible to adapt the communication of personal and psychological characteristics of the individuals, to inform their decision-making. The more individuals are correctly informed, the more they are free to choose between being tested or not for *BRCA1/2* germline mutations, the more the ethical balance between the benefits and risks of the genetic test will be reduced.

## Abbreviations

BRCA1: BReast CAncer 1 gene
BRCA2: BReast CAncer 2 gene
HAPA: Health Action Process Approach
HBOC: Hereditary Breast and Ovarian Cancer Syndrome
IEO: European Institute of Oncology
IU: Intolerance of Uncertainty
WLSMV: weighted least square mean and variance adjusted
